### Power and sample size calculations

3.7

Using results of Braden et al., a standard deviation of 8.3 points for the Oswestry Disability Index was used for effectiveness of mindfulness-based stress reduction in LBP patients [79]. An effect size of Cohen's *d* = 0.83 was calculated when using the reported minimal clinically important difference of a 10-point change [57,80]. Effect sizes ranging from 0.5 to 1.1 have been found previously for mindfulness interventions using outcome measures of pain and physical function in mechanically and neurologically derived LBP. The large effect sizes powered for in this study are considered acceptable due to the large effect sizes found in studies using MORE with multiple outcomes measures [35,36,41]. Using the GPower program (version 3.1.9.4) for *a priori t*-test sample size calculations using *alpha* = .05 yields 80% power to detect an effect of treatment of size *d* = 0.83, with a sample size of 48 participants. When adjusting for an expected retention rate of 80%, a total proposed sample size of 60 participants is required (*n* = 30 per group).

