### Statistical analytical plan

3.8

Participant descriptive information collected at baseline, including demographics, pain characteristics, physical function, QoL, depression, and trait mindfulness will be reported as mean (SD) or number (percent), as appropriate, for each study group. Likewise, changes from baseline to follow-up of each outcome measure will be reported as mean (SD) for each group.

*A priori* analytical modeling has been developed based on primary and secondary outcome measures and established relevant covariates. Relevant covariates (according to priority) include age, sex [7], change in treatment during study enrollment (as a binary variable), disease etiology [81,82], duration of symptoms prior to study enrollment, previous condition specific surgery [81], and baseline instrument score. To retain adequate power for linear mixed modeling, only covariates that are correlated to the outcome measure of interest (*r* ≥ .3, by Pearson or point-biserial correlation, as appropriate) will be retained. Covariates found to be significantly correlated will be added to the relevant model in a stepwise fashion in the aforementioned order.

All outcome variables aside from VAS pain (pain severity, physical function, QoL, depression symptoms, trait mindfulness, and reinterpretation of pain) will be analyzed using linear mixed modeling with maximum likelihood estimation of missing data to compare mean change between the MBI + TAU and TAU groups’. Next, we will evaluate associations between pain, physical function, QoL, depression symptoms, trait mindfulness, and reinterpretation of pain in relation to time spent practicing mindfulness amongst participants in the intervention group. The same approach will evaluate for significant differences in RMS and RMS-peak time within sEMG findings from baseline to follow-up. Finally, we will evaluate the association between changes in RMS from baseline to follow-up and change scores of the ODI, VAS, and PD-Q in participants in the intervention group.

For all models, we will complete a modified intention-to-treat analysis (mITT) including all those participants who completed the program. A per-protocol structure using only those participants in the treatment group who completed a minimum of 5 sessions synchronously will be used for sensitivity analysis as has been used previously in clinical trials and trials of MORE [41,83,84].

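### Adjustment for the baseline score is not guaranteed: it is last of seven covariates and must pass a correlation screen on the trial's own outcome data

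*Protocol article*

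**What the plan says.** Section 3.8 of the protocol article names the covariates in order of priority: age, sex, treatment change during the study, disease etiology, symptom duration, and then "previous condition specific surgery [81], and baseline instrument score". The baseline score is therefore seventh of seven.

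A screen follows: "To retain adequate power for linear mixed modeling, only covariates that are correlated to the outcome measure of interest" are retained. The threshold is r of at least .3, by Pearson or point-biserial correlation, with no absolute-value sign. The next sentence words the criterion differently: "Covariates found to be significantly correlated will be added to the relevant model in a stepwise fashion in the aforementioned order".

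The following paragraph says that the linear mixed models compare mean change between the two arms. No sentence places the baseline score in a model unconditionally. None says whether the screen is run on follow-up scores or on change scores.

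**The concern.** The baseline value of the same instrument is usually the best available predictor of the follow-up value, and here it has already been collected. A plan for about 48 completers would normally fix it in the model. Instead it ranks last and has to earn its place through a correlation estimated from the trial's own outcome data.

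Two things are at stake:

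- **Precision.** If baseline is left out, the treatment comparison has a larger variance than it needs.
- **A fixed model.** The modelling is presented as set in advance, yet which covariates it contains depends on the observed outcome data and can change between outcomes.

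The reason given, keeping adequate power, makes sense for weak covariates. For the baseline score it points the wrong way.

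**Working it through.** **Inputs from section 3.7 (Power and sample size calculations).** "An effect size of Cohen's *d* = 0.83 was calculated", and 80% power at alpha .05 is reached "with a sample size of 48 participants", that is 24 per arm. I take d as stated; how it was derived is a separate question. Rho is not given, so I assume 0.5 to 0.7 in the main, with equal variances at the two visits.

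**Step 1: the plan's own figure.** A two-sided two-sample t-test (noncentral t) at d = 0.83 needs 23.79, so 24 per arm, or 48 in all. Power at 24 per arm is 80.4%. Dividing by 0.8 for retention gives 60. Both stated sizes reproduce.

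**Step 2: variances, in units of the follow-up variance.**

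- Unadjusted change: 2(1 − rho)
- Follow-up adjusted for baseline: 1 − rho²
- Ratio, adjusted to change: (1 + rho)/2 = 0.75, 0.80, 0.85 at rho 0.5, 0.6, 0.7
- Patients needed by unadjusted change, relative to adjusted: 2/(1 + rho) = 1.33, 1.25, 1.18

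**Step 3: power at 24 per arm.** Section 3.7 does not say whether the SD behind d is that of scores or of changes, so both are shown.

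| rho | d in change SD units: change → adjusted | d in follow-up SD units: change → adjusted |
|---|---|---|
| 0.5 | 80.4% → 90.1% | 80.4% → 90.1% |
| 0.6 | 80.4% → 88.2% | 88.2% → 94.0% |
| 0.7 | 80.4% → 86.3% | 95.3% → 97.6% |

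At rho 0.7 the gain is therefore about 6 points in one unit and about 2 in the other.

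**Step 4: does baseline survive a screen on change scores?** With equal variances, corr(baseline, change) = −sqrt((1 − rho)/2) = −0.50, −0.45, −0.39 at rho 0.5, 0.6, 0.7.

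- *Signed rule, taken literally.* A negative correlation cannot reach +.3. In simulation (24 per arm) baseline passed in essentially 0% of trials.
- *Rule meant as |r| ≥ .3.* With no treatment effect, the Fisher z approximation at n = 48 gives a drop rate of 5%, 12% and 25% at rho 0.5, 0.6, 0.7. With d = 0.83 the treatment effect adds noise to the pooled correlation. Simulated drop rates are then about 9–10%, 18–20% and 32–37%, the ranges covering both units for d.

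**Step 5: a screen on follow-up scores.** The correlation is then positive. In 8,000 simulated trials per setting, with d = 0.83 in follow-up SD units and an unadjusted follow-up comparison wherever baseline failed:

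| rho | Baseline passes | Power, screened | Power, always adjusted |
|---|---|---|---|
| 0.3 | 44% | 81.7% | 83.2% |
| 0.5 | 90% | 89.0% | 89.7% |
| 0.7 | 99.9% | 97.3% | 97.3% |

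The largest loss is about 1.5 points. With no treatment effect, the rejection rate under this screen was 5.1% to 5.3%.

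**Step 6: the two criteria.** The two-sided 5% critical |r| is 0.285 at n = 48, so the .3 threshold and a significance test nearly coincide in the between-arm models. At n = 24, the size of the intervention arm alone, it is 0.404 and they do not.

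**The case against.** The best defence is that the harsh result in step 4 needs two choices the article does not state: that r keeps its sign, and that the screen is run on change scores. The text screens against the outcome measure and mentions change only later. It also allows point-biserial correlations, whose sign depends on how a binary variable is coded, so |r| is the sensible reading. If follow-up scores are screened, little is lost. All of this stands, and it rules out saying that the plan always excludes the baseline score.

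A reader might draw four other strong inferences that the document does not support:

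- **Chance baseline imbalance goes uncorrected.** If change is analysed, baseline has already been subtracted. What remains is inefficiency and a carry-over of (1 − rho) times the gap through regression to the mean.
- **Covariates are chosen after unblinding.** The article does not say so. The list, order and threshold are fixed, and the screen could be run on pooled data without arm labels.
- **Being seventh in itself keeps baseline out.** No stopping rule is given. If every covariate that passes is added, order does not alter the final model.
- **The screen inflates type I error.** The one-covariate simulation in step 5 showed no such effect.

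Limiting seven candidates with about 48 completers is also a defensible aim. That argument covers weak covariates, not the baseline score. A mixed model with a common baseline mean for both arms would largely remove the loss, but the article does not specify one, and listing baseline as a covariate fits that model poorly.

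**Conclusion.** The point holds as a matter of precision and of fixing the model in advance, not of validity. As written, section 3.8 does not guarantee baseline adjustment, allows the model to differ by outcome, and gives a reason that is wrong for the baseline score.

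The size is uncertain because it rests on rho, on equal variances, and on which reading of the screen is meant. It runs from about 1.5 points of power or less (screen on follow-up scores) to about 10 points at rho 0.5 and 2 to 6 points at rho 0.7 (screen on change scores, baseline dropped). Under an |r| rule on change scores the loss arises only in the trials where baseline fails the screen. That the result depends on an unstated reading is itself a reason to settle the wording.

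**What to change.** In every between-arm model, enter the baseline value of the same instrument as a prespecified covariate with the follow-up score as response. Alternatively, use a two-visit mixed model with a common baseline mean for both arms. In either case exempt baseline from any screen, and do not use it as response and covariate in the same model.

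Replace the correlation screen and stepwise entry with a short list of baseline covariates fixed in advance and used for every outcome. Treatment change during the study does not belong on that list, because it arises after randomisation and may be affected by the arm.

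The cost is analysis wording only. The baseline scores are already collected, and neither the sample size nor the visit schedule changes.

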Evaluation of daily VAS scores will be conducted using growth curve analysis with day 1 of the intervention for the respective cohort as the intercept to account for changes in VAS occurring between baseline and intervention initiation.

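### Maximum likelihood for the non-VAS mixed models slightly understates variances at 48 to 60 people; REML with small-sample degrees of freedom handles the missing data as well and holds 5%

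*Protocol article*

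**What the plan says.** Section 3.8 of the protocol article sets one approach for "All outcome variables aside from VAS pain": they are to be "analyzed using linear mixed modeling with maximum likelihood estimation of missing data", so that mean change can be compared between the two arms. The same section then refers to the same approach for the sEMG variables RMS and RMS peak time, which most naturally means the same kind of model. Daily VAS is handled separately: "Evaluation of daily VAS scores will be conducted using growth curve analysis", with no estimator named.

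The section lists seven candidate covariates. A covariate stays only if its correlation with the outcome is at least .3, and those kept enter stepwise. The modified intention-to-treat set is limited to people who completed the program. No reference distribution or degrees-of-freedom method is given.

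Section 3.7 gives the size of the trial. A t-test calculation "yields 80% power to detect an effect of treatment of size *d* = 0.83, with a sample size of 48 participants", raised to 60 (30 per group) for 80% retention.

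**The concern.** ML estimates a variance by dividing the residual sum of squares by the number of people, as if the fixed effects were known. REML divides by that number less the fixed effects fitted. In a large trial the difference vanishes; at 48 to 60 people it is small but visible. Standard errors come out too small, intervals too short and p-values too low.

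The plan ties ML to missing data. REML is also a likelihood method and rests on the same missing-at-random assumption, so that reason does not favor ML for the tests. The sample size in section 3.7 comes from a t-test, which uses the unbiased variance and t degrees of freedom. An ML analysis does not quite deliver the alpha of .05 assumed there.

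**Working it through.** **Inputs from section 3.7.** Alpha .05, power 80%, d = 0.83, 48 evaluable, 60 randomised, 80% retention.

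**The plan's own figure.** Taking d = 0.83 as given, a two-sided two-sample t-test has power 78.6% at 23 per arm and 80.4% at 24 per arm. That gives 48 in total, and 48/0.80 = 60. Both stated numbers reproduce. (Whether 0.83 follows from the stated SD and difference is a separate question and does not bear on this point.)

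**Formulas.** Let n be the number of people and p the number of fixed effects in the between-arm comparison of change. With complete data:
- ML variance divided by unbiased variance = (n − p)/n
- standard-error ratio k = √((n − p)/n)
- false-positive rate, ML with normal reference = 2·P(t on n − p df > 1.96·k)
- false-positive rate, ML with t reference = 2·P(t on n − p df > c·k), where c is the two-sided 5% point of t on n − p df

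**No covariates (p = 2: intercept and arm).**

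| n | variance ratio | k | ML, normal | ML, t | REML, normal | REML, t |
|---|---|---|---|---|---|---|
| 48 | 46/48 = 0.958 | 0.979 | 6.1% | 5.5% | 5.6% | 5.0% |
| 60 | 58/60 = 0.967 | 0.983 | 5.9% | 5.4% | 5.5% | 5.0% |

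At n = 48 with a normal reference, the interval half-width is 1.96 × 0.979 = 1.919 unbiased standard errors. The correct figure is 2.013, so the interval is about 5% too short. With a t reference it is about 2% too short. About half of the excess error comes from the variance and half from the reference distribution, so REML alone would not remove all of it.

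**Three retained covariates, one row per person (n = 48, p = 5).** This case applies if the outcome is the change score, or follow-up adjusted for baseline. The variance ratio is 43/48 = 0.896 and k = 0.946. The false-positive rate is 7.0% with a normal reference and 6.3% with a t reference.

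**Three covariates is an assumption.** The number that will pass the correlation screen is not known. The upper limit of the same formula, all seven kept as single terms (p = 9), gives 8.5% and 7.6%.

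**Two-visit model with covariates as main effects.** A covariate that is constant over time cancels out of each person's change, so it barely affects the arm-by-time test. In a simulation with n = 48, complete data, a random intercept and ML with a normal reference (1,500 runs each), the rate was 6.3% with no covariates and 5.8% with six. The Monte Carlo standard error was about 0.6 points, so the two do not differ.

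**Two-visit model fitted both ways** (no covariates, 2,500 runs each, Monte Carlo standard error about 0.5 points; the t reference uses the number observed at follow-up less 2):

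| Setting | ML, normal | ML, t | REML, normal | REML, t |
|---|---|---|---|---|
| 60 people, about 20% dropout depending on baseline | 5.8% | 5.2% | 5.2% | 4.5% |
| 48 people, complete | 6.6% | 5.8% | 6.0% | 5.2% |

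In the dropout setting the mean error of the treatment estimate was 0.0056 under both methods. REML therefore handled the missing data as well as ML did. Kenward-Roger and Satterthwaite degrees of freedom were not themselves simulated.

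**The case against.** The strongest reply is that the quoted words describe how missing data are handled, not how tests are done. On that reading the article leaves the fitting option and the degrees of freedom to a full protocol or analysis plan that is not shown. Part of this stands. The absence of a degrees-of-freedom method is not a fault in an article, and no normal-reference test is stated; that is why the size above is given for both references. But the sentence does name an estimator. An analyst who follows it would probably select ML where the software offers ML and REML as separate options, and the variance is then too small with either reference.

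A reader might infer more than the article supports:
- **That every mixed model is affected.** The sentence excludes VAS, and no estimator is named for the growth curve.
- **That error reaches 8% to 9% in the main comparison.** This needs one row per person and nearly all covariates kept. The plan screens them, and with a repeated-measures model they hardly matter as main effects.
- **That etiology adds several parameters.** The article gives no levels for it, and screening by Pearson or point-biserial correlation suggests continuous or binary terms.
- **That error reaches about 14% within the MORE arm.** That figure needs nine parameters in 24 people. The article says only that associations will be evaluated there and fixes no such model.

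It is also fair to say that ML has a proper use here. If the stepwise addition of covariates is judged by comparing likelihoods, ML is the right fit for that step.

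**Conclusion.** The point holds and is minor. Followed as written, the non-VAS models, and the sEMG models if they use the same method, would test at about 5.4% to 6.1% instead of 5% without covariates. About 6.3% to 7.0% is possible at n = 48 with three covariates, but only in a model with one row per person.

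This rests on three assumptions: that full ML is what the sentence means, that 48 to 60 people are analysed, and that the number of covariates kept is small. Treatment estimates agreed between ML and REML in the simulations; the effect is on standard errors, intervals and p-values. The article contains no contradiction or false figure on this point.

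**What to change.** In section 3.8, state that the non-VAS mixed models, including those for RMS and RMS peak time, are fitted by REML with Kenward-Roger or Satterthwaite degrees of freedom, and that tests and intervals are t-based. Both parts are needed. Keep ML only for comparing models that differ in their fixed effects. If missing data are the reason for a likelihood method, say that the REML analysis assumes outcomes are missing at random.

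The cost is one sentence and one software setting. P-values become slightly larger and intervals slightly wider. The sample size stays at 48 evaluable and 60 randomised, because the t-test calculation in section 3.7 already uses the unbiased variance and t degrees of freedom and gives 80.4% power at 48.

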### Study design

3.2

Baseline visits conducted at Helfgott Research Institute include confirmation of eligibility criteria, informed consent, study questionnaires, and sEMG collection for 20 gait cycles. Follow-up visits include all steps except repeated informed consent. All participants receive an email containing the informed consent document after baseline visit. Within 16 weeks of baseline visit completion, participants are randomized to either an 8-week MBI and treatment as usual (MBI + TAU) or TAU-only group to be completed in parallel cohorts. Both groups are asked to refrain from changes to their current treatment plan whenever reasonable (i.e., to avoid self-directed changes in treatment such as starting a new supplement) and to report any medically necessary (i.e., physician-recommended or -implemented) changes made during study enrollment. All study participants receive a copy of a pain education handout, “Understanding Pain,” at the time of intervention initiation as an effort to reduce the disparity upon health education [42]. This handout is provided publicly by the Oregon Pain Management Commission. Participants in both groups are asked to report daily pain levels using a Visual Analog Scale (VAS) administered via text message or email as preferred per participant.

Treatment as usual was chosen as the control condition for this experiment, as experts recommend using TAU control groups in studies of MBIs based on evidence from other RCTs conducted in this realm [43]. MORE has not been studied in the context of LR, and no gold standard has been identified as an active control for MORE in this subpopulation; therefore, TAU was deemed as appropriate for this study design. The control group undergoes TAU over 8 weeks of parallel group comparison and starts their 8-week enrollment period on the same day as the experimental group. Participants assigned to the TAU control group are offered to join a MORE program be delivered after the data collection period of the trial has ended. Our study team offered this option as we anticipate a benefit from MORE in the management of lumbosacral radiculopathy. A study flowchart can be seen in Fig. 1.

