To maintain anonymity, participants chose a “screen name” at their baseline study visit that is associated with them at session log in and participants were encouraged, not required, to participate in group discussion using their camera and microphone. Participants in the intervention group complete weekly activities and daily guided mindfulness practices via pre-recorded MP3 files at home consistent with the MORE protocol [34]. Audio from the synchronous sessions is recorded and stored securely for participants absent from synchronous sessions. Participants who do not attend sessions without providing advance notice to the study team will be contacted using the combination of communication methods to which they indicated they preferred at the baseline visit (i.e. phone, text, or e-mail). Attempts to contact the participant will be made until the participant has reached the maximum allowed number of missed sessions, at which point they will be declared lost to follow up. In addition to completing a daily VAS and reporting treatment changes, MORE participants are also asked to report their daily time spent practicing mindfulness. All adverse events occurring during the study, including those observed by or reported to the research team, will be recorded.

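### The analysis set labelled modified intention-to-treat admits only program completers, so no stated analysis keeps the randomised comparison

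*Protocol article*

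**What the plan says.** Section 3.8 (Statistical analytical plan) fixes one analysis set for every model: "we will complete a modified intention-to-treat analysis (mITT) including all those participants who completed the program". It names one other set, as a sensitivity analysis: "A per-protocol structure using only those participants in the treatment group who completed a minimum of 5 sessions synchronously". It mentions no analysis of all randomised participants.

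The same section says that outcomes other than VAS pain "will be analyzed using linear mixed modeling with maximum likelihood estimation of missing data to compare mean change" between the arms. Daily VAS scores go into a growth curve analysis.

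Two other sections matter. Section 3.4 (Intervention) describes what happens when MORE participants miss sessions without notice: contact attempts continue "until the participant has reached the maximum allowed number of missed sessions, at which point they will be declared lost to follow up". Section 3.2 (Study design) describes the other arm: "The control group undergoes TAU over 8 weeks of parallel group comparison". That arm has no sessions to attend or miss.

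**The concern.** An intention-to-treat comparison is protected because arm membership is set by randomisation and nothing that happens later changes who is counted. Here, being counted depends on completing something after randomisation. If those who stop differ in outcome from those who continue, and the filter acts differently in the two arms, the arms are no longer comparable even when treatment does nothing.

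In a mindfulness course, people who find it unhelpful, or who are doing badly, are plausible early leavers. Dropping them from MORE while keeping their counterparts in TAU would move the estimate toward MORE. The rule covers all models, the sensitivity analysis selects further in the same arm, and readers would see the result under an intention-to-treat name. This is a stated rule, not a detail left for a later analysis plan.

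**Working it through.** **1. The plan's own figures.** Section 3.7 gives alpha 0.05, 80% power and d = 0.83, leading to 48 evaluable participants, and 60 in total (30 per arm) at 80% retention. A two-sided two-sample t-test with the noncentral t distribution needs 24 per arm (power 0.804), so 48. Then 48 / 0.80 = 60. Both figures reproduce. The plan therefore expects up to 60 − 48 = 12 participants without outcome data, over both arms together.

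**2. Whom the filter removes.** The article does not define completing the program.
- *Reading A, completing MORE.* Where the article uses the word for something in this trial, it refers to MORE: the 8-week training program in section 3.4, and the MORE program offered to controls afterwards in section 3.2. The period common to both arms is called an enrollment period (3.2) or reporting period (3.3). TAU has nothing to complete, so the filter acts on MORE alone.
- *Reading B, completing the study.* Both arms are filtered and the asymmetry shrinks. The loss-to-follow-up rule in section 3.4 remains a way out that only MORE participants have.

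**3. Whether another stated analysis repairs this.** The at-least-5-synchronous-sessions set is also conditional on attendance and applies to the treatment group only. It cannot reveal a bias caused by selecting on attendance.

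**4. Fit with the missing-data method.** Maximum likelihood in a mixed model uses partial records. Removing non-completers first discards their baseline scores and any follow-up they gave. For the daily VAS, someone who leaves midway may have contributed weeks of usable scores. Section 3.3 already offers virtual completion of the follow-up questionnaires, so these people can be reached.

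**5. Possible size under Reading A.** The inputs are all assumptions: no true effect, 30 randomised per arm, a proportion q of MORE completing, no loss in TAU, and a correlation ρ between a latent tendency to complete and a better outcome. The documents give no value for ρ and no loss figure for MORE alone. Conversion to ODI points uses the SD of 8.3 from section 3.7.

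Bias toward MORE, in SD units = ρ · φ(z_q) / q, where φ is the standard normal density and z_q the q-quantile.

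For q = 0.80: z_q = 0.842, φ = 0.280, and 0.280 / 0.80 = 0.350, so bias = 0.350 ρ. Type I error comes from 40,000 simulated trials per row (two-sided t-test, nominal 5%).

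| ρ | Bias (SD) | ODI points (× 8.3) | Type I error |
|---|---|---|---|
| −0.3 | −0.105 | −0.87 | 6.8% |
| 0 | 0 | 0 | 4.9% |
| 0.2 | 0.070 | 0.58 | 5.5% |
| 0.3 | 0.105 | 0.87 | 6.4% |
| 0.5 | 0.175 | 1.45 | 9.5% |

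At ρ = −0.3 the bias runs against MORE, and only 0.9% of simulated trials falsely favour it.

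As a wider range, q = 0.60 gives 0.386 / 0.60 = 0.644, so bias = 0.644 ρ. For ρ = 0.2, 0.3 and 0.5 this is 0.129, 0.193 and 0.322 SD, with type I error of 7.0%, 9.5% and 18.6%. No passage suggests 40% non-completion.

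**6. Possible size under Reading B.** If both arms lose the same fraction with the same ρ, each mean shifts by the same amount and the difference is unbiased under no true effect. Bias then depends on how far loss, or its relation to outcome, differs between arms.

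**The case against.** The strongest reply is that the phrase is undefined in a condensed article. Because a separate 5-session rule defines the per-protocol set, the main set may simply mean people who finished the study in either arm. That is a fair reading, and it weakens any claim that only MORE is filtered. It does not rescue the rule: the set would still be conditioned on a post-randomisation event, would still carry an intention-to-treat label, and would still discard partial data.

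Three further objections stand.
- The 20% in section 3.7 is overall non-retention, not loss in MORE. Placing it all in one arm is an assumption.
- Direction depends on an unknown correlation. People who improve might also stop attending, and the bias would then go against MORE. At a correlation of 0.2 the type I error is close to nominal.
- Maximum likelihood is not made pointless. A participant may finish the sessions and still lack follow-up questionnaires. The virtual option does not cover sEMG, so sEMG can be missing among completers too.

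One objection bears on the remedy. If participants who reach the missed-session limit give no further data, redefining the set adds little in a two-visit model and leaves the result resting on a missing-at-random assumption. Outcome collection has to continue as well.

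**Conclusion.** The rule is wrong as written. The set governing all models is a completers set, the only alternative is narrower, and no stated analysis compares the arms as randomised. This follows from the text under either reading of program.

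A reader might infer more: that the analysis demonstrably favours MORE, that only the MORE arm is filtered, or that the false-positive rate is known to be inflated. The documents do not support these as facts. Bias toward MORE is the likely direction, because the natural meaning of program and the loss-to-follow-up rule both act on that arm. Its size ranges from nothing to about 0.175 SD (1.45 ODI points) for assumed correlations of 0 to 0.5 with 20% loss in MORE only. The correlation, the one-arm loss and the absence of a true effect are all assumptions. The article also labels no single primary outcome in section 3.8, so the point concerns all models rather than one primary test.

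**What to change.** - **Main analysis set.** Define it in section 3.8 as all randomised participants, analysed in their assigned arm whatever their attendance. Use the planned likelihood-based mixed model and the VAS growth curve with all available data.
- **Outcome collection.** State in section 3.4 that missed sessions do not count as loss to follow-up for outcomes. Keep inviting these participants to complete the follow-up questionnaires, virtually if need be, and the daily VAS.
- **Sensitivity sets.** Define completion explicitly and present the completer set as a sensitivity analysis beside the at-least-5-session set, without an intention-to-treat label.

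A complier-average effect with 5 sessions as its threshold is not recommended as the replacement. Section 3.4 gives absentees session recordings and gives all MORE participants home practice files, so those below the threshold may still receive MORE content.

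The cost is revised wording, some extra follow-up and slightly more analysis. The estimated effect may be smaller. Taking d = 0.83 as stated and outcomes from all 60, power is 0.885. If 20% of MORE participants do not complete and gain nothing (an assumption), d = 0.83 × 0.80 = 0.664 and power at 30 per arm is about 0.72. That loss is the real dilution from offering MORE to everyone assigned to it, which a completers set would hide.
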